# Electroacupuncture versus solifenacin for women with urgency-predominant mixed urinary incontinence: a protocol for a three-armed non-inferiority randomized controlled trial

**DOI:** 10.1186/s12906-019-2784-1

**Published:** 2020-01-23

**Keywords:** Acupuncture, Antimuscarinic drugs, Urge, Stress

## Abstract

**Background:**

Among women suffering from urinary incontinence (UI), about one-third are diagnosed with mixed urinary incontinence (MUI), among which urgency-predominant MUI causes more shame and inconvenience to patients. The treatments for urgency-predominant MUI have limited guidelines and previous studies have indicated that electroacupuncture (EA) might be a safe and effective option. The present study aims to evaluate the effect of EA on women with urgency-predominant MUI.

**Methods:**

The study is a multicentered, three-armed, non-inferiority randomized clinical trial. A total of 282 female patients with urgency-predominant MUI will be randomly divided into three groups, namely the EA group, sham electroacupuncture (SA) group, and solifenacin treatment group at a ratio of 1:1:1. Thirty-six sessions of acupuncture treatment over 12 weeks and solifenacin treatment over 36 weeks will be provided. The primary outcome will be the decrease of urgency urinary incontinence (UUI) episodes after 12-week treatment. Secondary outcomes will include changes in incontinence episodes, urinary frequency, urgency, severity of symptoms, and influence on quality of life, assessed using the International Consultation on Incontinence Questionnaire Short Form (ICIQ SF) and Overactive Bladder Questionnaire Short Form (OAB-q SF). All patients will be continuously followed up until week 36 and their allocations will be statistically analyzed.

**Discussion:**

Though placebo of solifenacin is rather difficult to access and all patients in the trial cannot be fully blinded, the present study will serve as an introduction of three-armed, randomized, non-inferiority, and sham acupuncture-controlled clinical trials to the acupuncture field, in an attempt to compare the effects of EA and solifenacin for treating women with urgency-predominant MUI.

**Trial registration:**

ClinicalTrials.gov: NCT03787654. Registered on 25 December, 2018.

## Background

Mixed urinary incontinence (MUI) is defined as a complaint of involuntary loss of urine associated with urgency, effort, or physical exertion or upon sneezing or coughing by the current International Continence Society guidelines [1]. The percentage of women suffering from the condition ranges from 14% to 61% [2]. It is regarded as urgency-predominant when a sudden sensation of voiding accompanied by uncontrolled incontinence is the dominant symptom [3]. Among women suffering from urinary incontinence (UI), about one-third have MUI with symptoms of both stress urinary incontinence (SUI) and urgency urinary incontinence (UUI) [4]. Urgency symptoms are more difficult to alter through lifestyle modifications or by controlling bladder activity than both stress-predominant MUI and balanced MUI symptoms [5, 6], resulting in more shame and inconvenience for women with urgency-predominant MUI. To relieve the symptoms, conservative treatments involving lifestyle interventions and behavioral and physical therapies are recommended by the European Association of Urology (EAU) guidelines, such as bladder training, electrical stimulation, and posterior tibial nerve stimulation. However, conservative treatments are often used as part of the treatment package because of uncertain effectiveness [4]. Other therapies for UI include surgical and pharmacological management. For urgency-predominant MUI, the success rate of surgery is 52%, 26% less than that for stress-predominant MUI [7]. Additionally, associated complications, adverse events and high costs also need to be considered when surgery is recommended. Solifenacin, the first-line medicine for urgency-predominant MUI, can reduce incontinence episodes in 24 h [8]. However, it can also induce common side effects of dry mouth, blurred vision, dry eyes, and constipation [4], and has a high medication discontinuation rate [9]. Consequently, alternative therapies with more effectiveness and safety urgently need to be explored.

Acupuncture might be a promising candidate for the treatment of urgency-predominant MUI. As previous research has indicated, electroacupuncture (EA) might be noninferior to pelvic floor muscle training (PFMT) plus solifenacin in reducing urgency incontinence episodes for women with MUI [10]. However, the trial included patients with stress-predominant MUI, urgency-predominant MUI, and balanced MUI rather than focusing on urgency-predominant MUI exclusively; hence, it is difficult to confirm whether EA is effective for the treatment of urgency-predominant MUI. In addition, the efficacy of EA cannot be clearly illustrated because of the lack of a sham acupuncture-controlled group. For this reason, the present study is a three-armed sham-controlled randomized trial aimed at evaluating the effects of EA and comparing the effects of EA and solifenacin in reducing urgency incontinence episodes for women with urgency-predominant MUI.

## Methods and analysis

### Study design

The study will be a multicentered, randomized, three-armed, non-inferiority clinical trial with sham electroacupuncture (SA) and solifenacin as controls. The null hypothesis is that the improvement (difference in the number of UUI episodes between baseline and 12-week assessment) in the EA group would be 50% or less of the difference in improvement between the solifenacin and SA groups; that is, noninferiority would be established if EA, compared with solifenacin, retains at least 50% of the efficacy of solifenacin over SA. The outcome assessors and statisticians will be blinded. Patients in the EA and SA groups will be blinded, while those in the solifenacin group will not be blinded. The study will be carried out after the ethics is approved by the Institutional Review Board. All the patients in the study will be informed about the details of the study and written informed consent will be obtained before enrollment.

In the written informed consent, the participants will be informed that if they are eligible and willing to participate in the study, they will be randomized into the EA group, SA group, or solifenacin group with the same probability. The investigators plan to enroll 282 participants, with 94 in each group. Solifenacin is an effective treatment for the UUI component, as recommended by the current guidelines, and our previous studies indicated that EA and SA are both effective for urgency-predominant MUI to some degree. In the EA group, participants will receive traditional EA at traditional acupoints, while participants in the SA group will receive shallow and minimal EA at non-acupoints.

The study is designed and reported in accordance with the Consolidated Standards of Reporting Trials (CONSORT) guidelines, the Standard Protocol Items: Recommendations for Interventional Trials (SPIRIT) Checklist, and Standards for Reporting Interventions in Controlled Trials of Acupuncture (STRICTA) recommendations. The protocol has been reviewed, revised, and supported by experts in statistics, urology, and acupuncture.

### Subjects

#### Sample size calculation

The sample size was calculated based on our previous study [10]. The expected drop-out rate is 10% and the noninferiority margin is 50% of the comparative efficacy between SA and Solifenacin. The noninferiority margin was set based on our hypothesis that EA will be associated with at least 50% of the difference in the efficacy of solifenacin as compared with that of SA.

#### Patient recruitment

This study will be conducted in six hospitals over China, specifically Guang’anmen Hospital, China Academy of Chinese Medical Sciences; Jiangsu Province Hospital of Traditional Chinese Medicine; Shanxi Province Hospital of Traditional Chinese Medicine; Guangdong Province Hospital of Traditional Chinese Medical; the First Hospital of Hunan University of Chinese Medicine; and Hengyang Hospital Affiliated to Hunan University of Chinese Medicine. Of the six hospitals, one plans to recruit 42 patients, while the other five plan to recruit 48 patients each. Patients will be recruited via newspapers, posters, and networking both from the surrounding communities and hospitals. All potentially eligible women with incontinence will be invited to participate in the trial, proceeding with a series of history taking, physical examination, specialist diagnosis, questionnaire, voiding diary, and laboratory examinations to screen and enroll the patients, as recommended by EAU guideline [4]. Eligible patients will be randomly placed in the EA, SA, or solifenacin treatment group.

Demographic information about age, marital status, menstrual status, education background, occupation, and medical history will be cautiously recorded at the baseline period. The International Consultation on Incontinence Questionnaire Short Form (ICIQ SF) and the Overactive bladder questionnaire short form (OAB-q SF) will also be used at the baseline period to assess the severity of incontinence symptoms and the influence on quality of life (QoL).

In the EA and SA groups, patients will receive 12-week treatment and 24-week follow-up, while those in the solifenacin treatment group will take the medicine for a succession of 36 weeks. Assessments will be carried out at the baseline, at 4, 8, and 12 weeks from the baseline in the treatment period, and at 24 and 36 weeks from the baseline in the follow-up period (Fig. 1 Study Flowchart; Table 1 Outcome Assessment Schedule).

**Fig. 1 Fig1:**
[figure not shown]
Study Flowchart. *The dose of solifenacin can be increased to 10 mg per day and can be discontinued following a comprehensive consideration of the state of incontinence symptoms and the side effects

**Table 1 Tab1:** Outcome Assessment Schedule

The assessment of timepoint						
Timepoint	Week 0	Week 4	Week 8	Week 12	Week 24	Week 36
Incontinence episodes in 72 h	X	X	X	X	X	X
Urgency incontinence episodes in 72 h	X	X	X	X	X	X
Stress incontinence episodes in 72 h	X	X	X	X	X	X
Other incontinence episode in 72 h	X	X	X	X	X	X
Urinary frequency in 72 h	X	X	X	X	X	X
Urinate episodes regarded as Grade 2 by PPIUS* in 72 h	X	X	X	X	X	X
Urinate episodes regarded as Grade 3 by PPIUS in 72 h	X	X	X	X	X	X
Nocturia episode in 72 h	X	X	X	X	X	X
Water input in 72 h	X	X	X	X	X	X
Pad consumption in 72 h	X	X	X	X	X	X
ICIQ SF* questionnaire	X	X	X	X	X	X
OAB-q SF* questionnaire	X	X	X	X	X	X
PGI-I* score				X		X
PGSC*		X	X	X	X	X
Expectance evaluation	X					
Blind effect evaluation				X		
Dose of solifenacin taken		X	X	X	X	X
Safety evaluation of acupuncture	X					
Adverse effect of Solifenacin	X					
Other adverse events	X					
Combination of medication	X					
Adherence evaluation	X					
Completeness of research	X					

Abbreviations: PPIUS: Patient perception of Intensity of Urgency Scale; ICIQ SF: International Consultation on Incontinence Questionnaire Short Form; OAB-q SF: Overactive bladder questionnaire short form; PGI-I: Patient global impression improvement; PGSC: Patient Global Symptom Control

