### Measures

#### Outcome assessment

##### Primary outcome measure

The primary outcome is the change in UUI episodes during an average 24-h period at 12 weeks from the baseline (after the first treatment), recorded in a 3-day voiding dairy.

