##### Secondary outcomes

UUI episodes, urinary frequency, urgency, nocturia, pad consumption, and volume drunk in an average 24-h period will be recorded in a 3-day voiding diary both during the treatment period (week 4, week 8, week 12) and the follow-up period (week 24, week 36). The 3-day voiding diary is a reliable, objective, and sensitive measurement recommended by EAU guidelines to monitor changes in incontinence. Urination, urgency, incontinence, drinking, and pads consumed are recorded. Urgency will be evaluated using the Patient Perception of Intensity of Urgency Scale (PPIUS), which is recommended by the European Medicines Agency [14]. Voiding at levels of 3 and 4 are regarded as urgency episodes [15], while levels 1 and 2 are regarded as normal or a strong desire to void [14].

In addition, the ICIQ SF and OAB-q SF scores will be applied as outcome measurements both during the treatment period (week 4, week 8, week 12) and follow-up period (week 24, week 36). The ICIQ SF is a questionnaire developed by the International Consultation on Incontinence [16] to evaluate the severity of incontinence and impact on QoL in the past 4 weeks. It contains four items: frequency, amount of leakage, impact of UI on QoL, and a separate item to indicate the cause of incontinence. The score is the sum of the first three items and the total score ranges from 0 to 21, with a higher score indicating worse symptoms and greater impact on QoL. A Chinese version has been translated and validated [17]. OAB-q SF is a validated questionnaire used to assess the burden of OAB symptoms and the effect on QoL in the past 4 weeks. The questionnaire includes items on coping, sleep, and emotional interactions [18]. The scores are transformed to a 0- to 100-point scale, with higher symptom-severity scores indicating worse symptoms and higher QoL scores indicating a better QoL. A Chinese version of OAB-q SF has also been validated [19].

Patient global impression improvement (PGI-I) will be applied in week 12 and week 36 to measure the effects of therapy subjectively. PGI-I is a scale ranging from 1 to 7, with 1 indicating very much better, 2 indicating much better up to 7 indicating very much worse [20].

Residual urinary volume will be retested with abdominal B-ultrasound in week 12 from the baseline.

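### Table 1 schedules counts of PPIUS Grades 2 and 3, while the text defines urgency on the same scale as levels 3 and 4, and nothing reconciles the two

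*Protocol article*

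**What the plan says.** Two places in the protocol article bear on how urgency is counted.

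- **Table 1, Outcome Assessment Schedule.** Two rows refer to the PPIUS: "Urinate episodes regarded as Grade 2 by PPIUS* in 72 h" and "Urinate episodes regarded as Grade 3 by PPIUS in 72 h". Each is marked at weeks 0, 4, 8, 12, 24 and 36. There is no row for Grade 4, and no separate row for urgency episodes.
- **Secondary outcomes.** Urgency is one of the listed diary outcomes: "UUI episodes, urinary frequency, urgency, nocturia, pad consumption, and volume drunk in an average 24-h period will be recorded in a 3-day voiding diary". The instrument is named: "Urgency will be evaluated using the Patient Perception of Intensity of Urgency Scale (PPIUS". The rule follows: "Voiding at levels of 3 and 4 are regarded as urgency episodes", whereas "levels 1 and 2 are regarded as normal or a strong desire to void".

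The table says *Grade* and the text says *level*. The article does not say whether they are the same numbering, and it does not give the lowest and highest category of the scale.

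**The concern.** The two PPIUS rows are the only urgency counts in the schedule, so one would expect them to be the categories that make up the urgency outcome. On their face they are not. A data manager who works from Table 1 and an analyst who works from the outcome text would count different sets of voids under the same name.

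Urgency is a named secondary outcome, and the Discussion gives the burden of urgency in this population as a reason for using the PPIUS. By the text's own rule, a level 2 void and a level 4 void are different events, so the two sets can give different counts and different contrasts between arms. Six hospitals contribute data and the Trial status section says recruitment has started. An ambiguity left open now would have to be settled once data exist.

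**Working it through.** No sample size, power or error-rate figure is involved, so the check is a comparison of category sets.

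**Inputs**

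- Scheduled categories (Table 1): T = {2, 3}
- Categories counted as urgency (Secondary outcomes): U = {3, 4}
- Categories not counted as urgency (Secondary outcomes): N = {1, 2}

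Table 1 counts over 72 h and the text reports an average 24-h period. That is a division by 72/24 = 3 and plays no part in the discrepancy.

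**Reading A: *Grade* and *level* are the same numbering**

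- In both T and U: {3}
- In T but not U: {2}, which belongs to N
- In U but not T: {4}, the highest level the article names

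The scheduled counts then include one non-urgent category and lack one of the two urgent ones.

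**Reading B: the table numbers the scale one step lower (level = grade + 1)**

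This is an assumption; the article does not state it.

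- Grade 2 becomes level 3 and Grade 3 becomes level 4, so T maps to {3, 4} = U
- The scheduled rows are then the right ones, and only the labels differ
- If the text's cut-off of 3 and 4 is applied to table-numbered data, Grade 3 is level 4 and Grade 4 would be level 5, a level the article does not name
- That selection drops level 3 voids (Grade 2), which the text counts as urgency

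**Comparison.** Under A the schedule does not match the definition. Under B it does, but the article uses two numberings for one scale without saying so, and combining them goes wrong. Neither reading leaves table and text usable together as printed.

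**Reach.** The primary outcome is defined separately: "The primary outcome is the change in UUI episodes during an average 24-h period at 12 weeks from the baseline". It has its own row in Table 1 (urgency incontinence episodes) and does not use the PPIUS rows. The sample size section and the retention-of-effect test do not use them either.

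**The case against.** The strongest reply is that Table 1 is a schedule and not a definition. Its PPIUS rows are two separate counts, neither is labelled urgency, and nothing says they are added together. An urgency episode is defined only in the Secondary outcomes section, which also places urgency in the 3-day diary. Both places pick two adjacent categories, and a shift of one makes them coincide exactly, so a difference in numbering is a plausible explanation. The article condenses a fuller protocol, and the CRF is not shown. Finally, the Statistical analysis section treats everything beyond the primary analysis as descriptive.

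Most of this stands, and it limits the point. A reader might infer that the urgency endpoint will count non-urgent voids and lose the most severe ones, at six of six visits for all 282 patients. The article does not support that:

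- it nowhere says the endpoint is built from the Table 1 rows;
- a numbering shift is not excluded;
- the figures for visits and patients describe the planned schedule and enrolment, not voids shown to be misclassified.

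The reply does not remove the inconsistency. Condensation explains missing detail, but here the article makes two statements that do not agree. The numbering shift is a guess until the sponsor confirms it, and if it is true the text and the table still need a common numbering.

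**Conclusion.** The inconsistency is real and sits in the current text of both places. The literal overlap is one category of two: the schedule has {2, 3} and the definition has {3, 4}. Whether this is a mismatch in what is counted or only in labels depends on the scale's numbering, which the article does not give.

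The effect is confined to the secondary urgency outcome, and no stated figure changes. Whether a correct count can be recovered depends on the diary holding a PPIUS grade for each void. The article implies this by recording urgency in the diary and evaluating it with the PPIUS, but does not state it. The point should be corrected because the outcome is named and the correction is small. It does not threaten the trial's main conclusion.

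**What to change.** 1. Use one PPIUS numbering in Table 1 and in the Secondary outcomes section, with one term (*grade* or *level*), and state the lowest and highest category.
2. Make the Table 1 rows match the categories that the Secondary outcomes section defines as urgency. If the table's numbering is kept, restate the text's cut-off in that numbering.
3. Check that the CRF and the EDC system use the same numbering and capture every category in the definition. Neither is shown, so this is a check and not a presumed error.
4. Apply the single definition at all six timepoints, including visits already recorded where the diary holds each void's grade. Where it does not, say so and report what can be derived.

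The cost is an edit to one table and one paragraph, a check of the CRF and EDC and, if needed, a corrected derivation. No new assessment is required if each void's grade is already recorded.

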#### Inclusion criteria

Female patients diagnosed with MUI in accordance with EAU guidelines, determined by history taking, physical examination, and specialist diagnosis [11];Age between 18 and 80 years old;Urge index greater than stress index, determined with the Medical, Epidemiologic, and Social aspects of Aging (MESA) questionnaire [12];At least four episodes of UUI in a 3-day voiding diary;UUI episodes dominate more than 50% of the total incontinence episodes in the 3-day voiding diary;Positive cough stress test;A voluntarily-signed written informed content.

#### Exclusion criteria

Having pure SUI, pure UUI, overflow UI, or neurogenic bladder;Uncontrolled urinary tract infection;Tumor in urinary system or pelvic organs;Pelvic organ prolapse ≥ degree II;Residual urine volume ≥ 100 ml;Maximum flow rate<15 ml/s;Receiving treatment of acupuncture or positive medications targeted at incontinence, such as antimuscarinic drugs, in the past 1 month;Underwent anti-incontinence or pelvic organ surgery, including metrectomy;Complications of severe diabetes or hypertension;Complications of diseases in the nervous system that could hamper hypourethral function, such as multiple sclerosis, senile dementia, Parkinson’s disease, spinal cord injury, cauda equina nerve injury, and multiple system atrophy;Severe complications in the cardiac, lung, cerebrum, hepatic, or renal system, psychonosology and coagulation function, or obvious cognitive disability;Installation of a cardiac pacemaker;Allergy to solifenacin or contraindications to antimuscarinic drug, including urinary retention, gastrointestinal peristalsis paralysis, myasthenia gravis, ulcerative colitis, and angle-closure glaucoma;Allergy to metal or intolerance to EA stimulation;Pregnant or planning to conceive in the next 1 year or delivered within the past 1 year.

#### Randomization

Randomization will be performed by an independent third party, Linkermed Technology Co. Ltd. (Beijing, China). Randomization sequence will be generated by computers in varying block sizes and stratified by centers, and central randomization system will be adopted to conduct the process. Once the patient is confirmed eligible to be enrolled, the study coordinator in charge of the randomization will log into the central randomization system to obtain the allocation information. Patients will be randomly allocated into the EA group, SA group, or solifenacin treatment group at a ratio of 1:1:1.

#### Blinding

Patients will be informed that they might be allocated to one of the three groups before enrollment. Patients in the EA and SA groups will be unaware of the allocation while those in the solifenacin group will not be blinded. The procedures for SA will be identical to those for EA, except that needles will be inserted into non-acupoints shallowly, with no manipulation, no sensation of *deqi,* and a minimal electric current. Patients will be treated separately to prevent communication. After 12-week treatment, the blinding effect will be evaluated.

Except for the acupuncturists, the principal investigators, co-investigators, research assistants, outcome assessors, and statisticians will all be blinded to the allocation.

